### 3.4.2 Individual-randomised trial of household support

The unit of randomization will be an individual attending each clinic, and not households, however, the trial outcomes will be evaluated at the level of the clinic to cater for any clustering at clinic (suburb) level. The main differences between the two arms will be:

- Proportion on ART with treatment failure defined as an HIV-1 viral load >400copies/ml at 12 months after starting ART or death in the first year of ART
- Proportion who miss two or more *routine* appointments by the end of two years of follow-up

Other comparisons between arms will include:

1. all-cause mortality
2. numbers of and time to first hospital admission (defined as stay in hospital for ≥24 hours)
3. numbers of additional attendances (over and above routine follow-up) to PHC
4. proportion of children who have an average adherence rate <80% 12 months after starting ART
5. proportion of children who change to 2nd line ART as defined by National Guidelines (due to reasons not related to toxicity, side-effects or starting TB treatment)

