## 4.5 Participant selection, inclusion and exclusion criteria

The inclusion criteria for participation in the trial will be:

- age between 6 years (day of their 6th birthday and older) and 15 years (a day before their 16th birthday)
- test HIV-positive following PITC in the PHC
- willing to have their HIV care at the PHC
- usual residence in the study suburb where the PHC is located
- informed consent by parent and assent from child to participate

The exclusion criteria for participation in the trial will be:

- age <6 years or ≥16 years
- usual residence outside the study suburb where the PHC is located
- previously tested HIV+ positive and receiving care (clinical or psychosocial)
- not planning to access HIV care at the PHC

All participants enrolled into the trial will automatically be offered enrolment into the cohort study. Additionally, any children aged 6-15 years who test HIV-positive following PITC after enrolment for the trial is completed, will also be approached for recruitment into the clinical cohort study.

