# HOUSEHOLD-LEVEL VLW SUPPORT

Community-based adherence support will be provided to families enrolled in the ZENITH trial by Voluntary Lay Workers (VLW) who will be recruited and trained to offer psychosocial counselling, practical advice, and links to appropriate referrals. The exact structure of the intervention, including guidelines and protocols specifying the nature and frequency of activities provided by VLWs, will be determined following the formative research described in Section 5.4, which will identify locally important facilitators and barriers experienced by the primary caregivers of HIV+ children. However, the LHW programme will centre around a series of home visits to (1) assess each enrolled family’s circumstances and needs; (2) identify feasible measures that caregivers might put in place to maximise engagement with care; (3) offer both general support and tailored assistance, following standardised guidelines; and (4) refer families to locally available organisations offering additional support services. Finally, LHW will serve as a link to the HIV treatment services by reminding caregivers of scheduled appointments, and following-up with clinic staff to check families’ attendance and identify emerging concerns that could lead to attrition from care.

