## 6.2 Duration of intervention

The LHW intervention will be implemented over eighteen months. As new patients are enrolled in the clinic, their permission will be requested for referral to a LHW for an initial home visit. LHW will conduct a standardised assessment and describe the support and referrals provided through the project; new families enrolled in the study clinics will be visited following the same schedule as clinic appointments, namely once a fortnight for the first month, every 4 weeks in the following 2 months, and subsequently every 3-months. Children who are not yet eligible for ART will receive the same schedule of home visits, to encourage retention in care during the routine monitoring phase. Once they become eligible and initiate ART, the first 3 home visits will be repeated to deliver the activities related directly to treatment issues.

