## 7.2 Cohort study data collection

Patients who test HIV positive and choose to register for HIV care at the PHC will be invited for an initial assessment within a week of diagnosis. The assessment will include:

- Record of social history: Current household structure, family history, type of guardianship, knowledge of HIV status, schooling
- Review of clinical history: HIV testing history, past infections including TB, other significant illness, hospitalisations, HIV testing history
- Clinical assessment: standardised symptom screen, WHO clinical stage
- Examination: standardised clinical examination, growth assessment, lung function assessment
- Tests: CD4 count, blood sample store

Patients will be referred for counselling and started on cotrimoxazole prophylaxis, and followed up two weeks later for assessment of ART eligibility (according to National Guidelines).

Those who are not eligible for ART will be followed up a month after the initial assessment, and then on a three monthly basis. At each visit, patients will have a brief symptom screen and undergo measurement of height and weight. Cotrimoxazole will be given and patients will have brief counselling. If participants start ART during the follow-up period, they will require an additional visit 2 and 4 weeks later, before reverting back to their follow-up schedule.

Those who are eligible for ART will be referred for counselling and started on the recommended first-line treatment. They will be then followed up at 2 weeks, and then monthly for 2 months and three monthly thereafter. At each visit, they will have a brief symptom screen, assessment of adherence, and measurement of height and weight. ART dose will be checked at each visit and adjusted according to weight.

For all participants, a CD4 count, growth and lung function assessment will be performed every 6 months, and psychosocial assessment (knowledge of HIV diagnosis, guardianship, schooling, disclosure to others) and pubertal staging carried out annually.

Participants who miss scheduled appointments will be offered alternative appointments for clinical review at the next available date. All participants will be followed up for 72 weeks. Participants recruited earlier in the study will continue to receive 3 monthly cohort follow-up until the study ends. At the end of the follow-up period, all participants will continue to receive their routine HIV care at the respective PHCs.

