### 9.2.2 Trial

The cumulative total number of children aged 6-15 years offered PITC who test HIV-positive and are recruited into the study under the trial arms will be determined.

The following data on the children who test HIV positive through PITC will be collected on study forms:

- Recruited or not recruited into the study
- Study arm recruited
- Routine clinic appointment dates on the clinic card and the actual visit date
- Any additional study visits
- On ART or not started
- Date started on ART
- CD4 count
- Viral Load post 12months ART
- On first vs second-line ART
- Pill count
- Adherence assessment result

Further, HIV-positive participants in each arm started on ART and date started will be used to determine if the participant has been on ART for a period of one year or more. The cumulative total number of participants who have been on ART for a period of ≥1 year will be determined.

A field will be generated which calculates the number of days between the routine appointment date and the actual routine visit date. If the difference is more than 7 days, an appointment will be classified as missed. The cumulative number of missed appointments for each participant will be calculated; the proportion of participants with more than two missed appointments will then be calculated for each arm.

Another ART outcome field will be generated which determines if the viral load is >400 copies/ml or if the participant has died within a period of one year on ART. If this is true, the ART outcome will be classified failure otherwise it will classified as success or unknown if the participant is lost to follow-up.

If the patient has not attended for an appointment for a period of >6 months, they will be followed up to ascertain the cause of this (death/move out of area/default /other). If alive and still in the area, cause of default will be determined as well as relevant clinical information. If agreeable the current viral load will be determined and the participant encouraged to re-attend for HIV care.

If the participant has died and the family is still in the area, the date of death will be recorded and a brief verbal autopsy conducted to ascertain the cause of death.

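### Section 9.2.2 traces absent children only after six months and no closing vital-status check is described, so late deaths are likely to be under-counted in the control arm

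*Protocol*

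**What the plan says.** **Tracing.** Section 9.2.2 states: "If the patient has not attended for an appointment for a period of >6 months, they will be followed up to ascertain the cause". If the child has died and the family still lives in the area, the date of death is recorded and a verbal autopsy is done. Before that point, section 7.2 says only that a missed visit leads to the offer of another appointment. The follow-up box of Figure 1.1 lists a family interview about cause of death for all children, but not how a death first becomes known.

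**Length of follow-up.** Section 7.2 says: "All participants will be followed up for 72 weeks", and adds: "Participants recruited earlier in the study will continue to receive 3 monthly cohort follow-up until the study ends". Section 1.5 has trial and cohort outcomes captured over eighteen months. Section 3.4.2 counts missed appointments "by the end of two years of follow-up". The 72-week schedule belongs to the cohort, which trial children may decline: "All participants enrolled into the trial will automatically be offered enrolment into the cohort study".

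**Contact by arm.** Under section 6.2, intervention families are "visited following the same schedule as clinic appointments", which means every three months after the first three, in a programme lasting eighteen months. Section 6 also has the lay worker check attendance with clinic staff and "identify emerging concerns that could lead to attrition from care". Figure 1.1 gives control children clinic visits only.

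**Outcomes that use death.** Section 3.4.2 lists "all-cause mortality" among the other comparisons between arms. It also counts death in the first year of ART within the treatment-failure outcome. Section 9.2.2 classes the ART outcome of a child lost to follow-up as unknown.

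**The concern.** A death can be counted only if someone learns of it. For a control child who stops attending, the plan describes no contact until more than six months have passed. For an intervention child, a lay worker is due at the home about every three months and also checks attendance. The chance of learning of a death therefore depends on the intervention itself, and most strongly near the end of follow-up, where the six-month trigger arrives too late.

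If late deaths are found more completely in the intervention arm, the intervention looks worse on mortality than it is, or a real benefit is hidden. The defect lies in what is collected, so no analysis can repair it afterwards. Delay also costs information, because the date of death is recorded only if the family is still in the area.

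**Working it through.** **The plan's own figure.** The protocol states no mortality rate and no power for mortality. The only power figure for an outcome that includes death is 87%, for 50% against 30% treatment failure or death with 123 children per arm (section 11.2.1). Assume a two-sided 5% test, with pooled proportion 0.40:
- standard error under no difference = √(2 × 0.40 × 0.60/123) = 0.0625
- standard error under the alternative = √((0.25 + 0.21)/123) = 0.0612
- without continuity correction: (0.20 − 1.96 × 0.0625)/0.0612 = 1.27, power 89.8%
- with the difference reduced by 1/123: 1.14, power 87.2%

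The stated figure is reproduced with the correction, and this point does not dispute it.

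**When the trigger is reached.** Six months is 26.1 weeks and eighteen months is 78 weeks. The later visits in Table 7.1 are at weeks 24, 36, 48, 60 and 72. Counting from the last attended visit:

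| Last seen | Trigger reached | By week 72? | By week 78? |
| --- | --- | --- | --- |
| Week 36 | 62.1 | yes | yes |
| Week 48 | 74.1 | no | yes |
| Week 60 | 86.1 | no | no |

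Deaths out of reach of tracing within the window:
- 72 weeks: after the week 48 visit, 24/72 = 33%
- eighteen months: after week 60, 18/78 = 23%

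Section 9.2.2 does not say when the six months start. Counted from the first missed visit, a child last seen at week 36 first misses week 48 and reaches the trigger at week 74.1. With 72 weeks, deaths after week 36 are then out of reach: 36/72 = 50%.

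**Effect on the mortality ratio.** These assumptions are not in the protocol: equal true mortality in the arms, constant hazard, all intervention deaths found, and control deaths found only while tracing can reach them. The apparent intervention-to-control ratio is then 1/(1 − share missed).

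| Window (six months from last attended visit) | No informal capture in controls | Half of late control deaths learned informally |
| --- | --- | --- |
| 72 weeks | 72/48 = 1.5 | 72/(48 + 12) = 1.2 |
| Eighteen months | 78/60 = 1.3 | 78/(60 + 9) = 1.1 |

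With the six months counted from the first missed visit, 72 weeks and no informal capture, the ratio would be 72/36 = 2.0.

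**Number of deaths.** With 175 controls and assumed 72-week mortality of 5%, 175 × 0.05 = 8.75 deaths occur, 8.75 × 48/72 = 5.8 are found and 2.9 are missed. Over an assumed range of 3% to 8%, 1.8 to 4.7 are missed.

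**If there is a real benefit.** Section 2.4 cites a cohort with mortality of 3.7% with home visits and 8.0% without, a ratio of 0.46. With a third of control deaths missed, this would appear as 0.4625 × 1.5 = 0.69.

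**Death in the first year of ART.** If ART starts at week 0, only weeks 48 to 52 are out of reach by week 72: 4/52 = 8%. For a child who starts at week 20 (an assumed example) and reverts to the existing visit schedule as section 7.2 describes, the first year ends at week 72, and weeks 48 to 72 are out of reach: 24/52 = 46%.

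**The case against.** The strongest counter-arguments, and what stands of each:

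- **Follow-up may be longer.** The 72 weeks are a minimum, early recruits continue to the end of the study, and section 9.2.2 sets no end to tracing. A child last seen at week 48 meets the rule only two weeks after week 72. With two years and three-monthly visits continuing, a child last seen at week 72 is reached at week 98. If each family's home visits also stop at eighteen months, the arms then differ little. This stands, and it makes the size uncertain. But no text says that tracing continues either, and the gap remains at eighteen months.
- **Tracing still works late in follow-up.** A reader might infer that the rule cannot operate at all in the last third of the 72 weeks. It can: a child last seen at week 36 is reached at week 62. Only absences that begin late escape.
- **Detection by lay workers is inferred.** No section gives them a duty to report deaths. A reader might take it as established that control deaths are the ones missed. The documents support that only as the likely direction, because a worker visiting the home would be expected to learn of a death.
- **Deaths are recorded for all children.** Figure 1.1 and section 9.2.4 say so, and the trial SOPs (Appendix 18.4) are not shown. But neither place says how the death of an absent child is first detected.
- **The main ART outcome is little affected.** This is correct when ART starts early.
- **Late safety reports in controls only.** A reader might infer this too. Section 9.3 does not say when its 10 days begin, so the documents do not support it.

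**Conclusion.** The point holds in a limited form. Under the protocol as written, an absence that begins late cannot trigger tracing before a 72-week or eighteen-month follow-up ends. No common vital-status check is described at the end, and home contact exists in one arm only. Control deaths are therefore likely to be under-counted, which works against the intervention. All-cause mortality is affected most. Death in the first year of ART is affected less, mainly in children who start ART late.

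With no true difference, an apparent mortality ratio of about 1.2 to 1.5 over 72 weeks (1.1 to 1.3 over eighteen months) is an illustration, not an estimate. It rests on full capture in the intervention arm, a constant hazard, and half or no informal capture of late deaths in controls. The 1.5 is the upper end when the six months run from the last attended visit, and it amounts to about three deaths at an assumed 5% mortality. No sample-size figure changes. The correction is cheap enough to be worth making despite the uncertain size.

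**What to change.** Add to section 9.2.2:

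- One vital-status check at the end of each child's trial follow-up, for every child in either arm not seen at the last scheduled trial visit. Research staff, not lay workers, do it, with the same method and form in both arms.
- A rule that deaths are counted by date of death within a fixed window whose length is stated, with the source of information recorded so that deaths known only through a lay worker can be identified.
- A statement of whether the six months run from the last attended or the first missed visit.

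The cost is protocol wording plus about 35 contact attempts (10% of 350, using the loss assumed in section 11.2.1). Because the check comes at close-out, it adds no support to the control arm during follow-up.

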### 9.2.3 Post-PITC HIV Prevalence Survey

Participants’ guardians will be asked if they know their child(ren)’s HIV status and whether their child(ren) is/are on cotrimoxazole or ART. Data on whether a selected participant has accepted or refused anonymous HIV testing will be collected, as well as number of visits required before a guardian is identified. The following will be determined:

- Cumulative total of all participants found to be HIV-positive on anonymous HIV testing, who were known to be HIV-positive prior to the survey
- Cumulative total of all participants found to be HIV-positive on anonymous HIV testing, who were previously undiagnosed
- Cumulative total of all participants who were known to be HIV positive and are not currently on currently on cotrimoxazole or ART

### 9.2.4 Cohort Study

The following data will be recorded for participants enrolled in the cohort study:

- ART status
- CD4 count
- Weight, height, MUAC, HC, pubertal stage
- FEV1, FVC and FEV1: FVC
- Incident opportunistic infections, including TB
- Hospitalisations
- Deaths
- Side-effects of ART
- Adherence
- School attendance rates
- Disclosure
- Type or guardianship

## 9.3 Adverse Event Data Collection and Management

No serious adverse events (SAEs) are anticipated, but forms and a reporting protocol are in place, and any event deemed to be a serious adverse event will be reported to the Medical Research Council of Zimbabwe and the IRB of BRTI within 10 days.

The following incidents will also be systematically recorded and reported back to the respective IRBs: -

- breach of confidentiality following HIV diagnosis
- negative life-events following participation or HIV diagnosis
- withdrawal from participation in the study by patients
- needlestick injuries

# DATA COLLECTION AND MANAGEMENT

## 10.1 Data management

Data will be managed at the project offices in Biomedical Research and Training Institute. Data analysis will be carried out in-house in collaboration with LSHTM statisticians.

Data collection and entry will be as detailed in the SOPs (Appendix 18.8). All data will be entered into a Relational Access Database, using Optical Character Recognition (OCR) of paper forms, with validity checks before scanning, and a protocol for verification of scanned records.

Inconsistencies will be investigated and resolved. Trial and other data will be analysed in the interim and on completion of each respective stage of the study, with the aim being to have all data verified, double entered, checked and resolved according to the data analysis plan (Appendices). The final analyses will then use the combined study data.

Protocols for managing data without breach of confidentiality are in place. Access to the final data set will be limited to the Data Manager ([name]), PI ([name]) and the LSHTM statistician ([name]). Sensitive information (including HIV results) will not be linked to personal identifiers in the final data set.

Data files will be kept in locked offices at BRTI during data entry, and in a locked data repository room for longer term storage.

## 10.2 Data capture forms and questionnaires

These are shown in the Appendices 18.2 to 18.7.

## 10.3 Data security

Hard copies of data and study documentation will be kept in locked offices, and long term storage will be in locked cupboards in a locked repository.

Electronic copies of data will be saved in password-protected files. NAS (Network attached Storage) Backup (http://www.nasbackup.com/index.php/Introduction) will be used to back data from PC onto NAS drives in a way that only the file differences are backed up every day. Additional permanent archives will be created by periodically backing up the data to two external hard drives every month. The hard drives will be stored in a locked filing cabinet away from the office by the PI.

## 10.4 Quality assurance

Data are checked for internal inconsistencies during verification and following data entry. Quality assurance protocols will be in place for each stage of the study, as detailed in individual SOPs.

# STATISTICAL CONSIDERATIONS

## 11.1 Assumptions re. survival of HIV-infected children

Data from prospective cohort studies in industrialised countries with follow-up beyond five years of age in the pre-ART era showed two patterns of disease progression in infants, rapid and slow progression. These data showed that approximately 20-30% of infected infants were rapid progressors and mortality approaches 100% by two years of age in this group. In the remainder, progression was much slower, with a substantial minority expected to survive childhood even without diagnosis and treatment.74-81 In Africa, there have been no natural history cohort studies assessing disease progression beyond five years of age.

A pooled cohort analysis estimated that the available data are most compatible with about one third being slow progressors whose median survival is at least 8 years with no upper limit to this estimate possible from the existing data.9 The remainder (fast-progressors) have high early mortality (median survival <2 years). Current estimates derive from survival models that combine the estimate of a third of vertically-infected infants being slow progressors with an assumption that median survival among this group will approximate that observed in children infected parenterally (i.e. approximate median survival of 16 years).10, 12 This equates to a 28% overall probability of HIV-infected infants surviving to 10 years, with approximately 1-3% of adolescents expected to be living with vertically-acquired HIV in Southern Africa.12

The main limitation of these models is that the median survival is extrapolated from that of children from developed countries infected through parenteral transmission, whose survival may well be quite different from those of vertically-infected slow-progressors in Africa. However, the projections are compatible with observed epidemiological data, suggesting that the model estimates provide a reasonably close approximation of the true natural history. In recent years, national population-based surveys in Southern Africa, however, have consistently reported high HIV prevalence rates of between 1-5% among older children.12, 82-85

For this project, it will not be possible to conduct an HIV prevalence survey prior to implementing PHC-based PITC, to investigate the burden of undiagnosed HIV. However, based on projections of HIV prevalence and the age distribution of children in HIV care in Zimbabwe, it is estimated that 80% of older children living with vertically-acquired HIV are currently undiagnosed.8, 12, 14

